## Abstract

**Background:**

Fibromyalgia (FM) is a syndrome most prevalent in women, in whom it is characterized mainly by chronic pain. An important issue is that many patients with FM are reported to have temporomandibular dysfunction (TMD), and the coexistence of these pathologies generates a clinical outcome of high complexity. The literature is unclear regarding an effective therapy for reducing pain in patients with both comorbidities. Exercise training and phototherapy (low-level laser therapy with light-emitting diode) are two of the approaches used to treat pain. Thus, the aim of this study is to assess the potential role of exercise training plus phototherapy in reducing chronic pain in women with FM and TMD. A further aim is to determine whether the interventions can improve quality of life and modulate endogenous serotonin.

**Methods/Design:**

A randomized controlled clinical trial will be conducted. It will involve 60 women ≥ 35 years of age with a diagnosis of FM and TMD. After recruitment, patients will be randomly allocated to one of four groups: a control group (no intervention), a group that will receive a phototherapy intervention (PHO), a group that will be prescribed muscle-stretching, aerobic, and facial exercises (EXT), or a group that will receive phototherapy plus exercise interventions (PHO + EXT). The trial will last 10 weeks, and the following outcomes will be evaluated on two separate occasions (baseline and within 24 h after the last day of the protocol). Pain intensity will be analyzed using a visual analogue scale and the McGill Pain Questionnaire, and pain thresholds will be punctuated using a digital algometer. FM symptoms will be assessed using the Fibromyalgia Impact Questionnaire, and quality of life will be determined with the 36-item Short Form Health Survey. Serotonin levels will be evaluated in salivary samples using a competitive enzyme-linked immunosorbent assay.

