### Interventions

The trial will be 10 weeks long, during which time patients will undergo two sets of phototherapy, exercise, or placebo procedures per week. Phototherapy will be applied 30 min before each exercise bout, and treatment sessions will be carried out Tuesdays and Thursdays each week. For eligible patients, the research will record outcome parameters at baseline prior randomization and 48 h after the last day of intervention. This evaluator will be blinded to the allocation of the patients into the respective groups.

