### Phototherapy

Phototherapy will be carried out with a PainAway™ nine-diode cluster portable device (Multi Radiance Medical, Solon, OH, USA). This portable device was specifically designed for pain relief and has two operating modes: mild and severe. Because of the characteristics of pain that patients with FM, we decided to use the device at the mild setting. The device has two identical application hand pieces—one active tip and the other for placebo procedure without energy, both equipped with a similar sound device. These equipment pieces are required to blinding applicator research and patients. Thus, the researcher who will apply phototherapy and the patient will not know which tip was used (active or placebo). The irradiation will be applied only in the tender points in which pain has been reported by the participants. These tender points can be occipital, cervical (near the C7), trapezius, supraspinatus, second costochondral joint, lateral epicondyle and gluteal/sacrum, and greater trochanter on the medial knee border. The temporomandibular joint (bilaterally) will be another irradiation target because of TMD. Each point will be irradiated for 300 s, in which 39.3 J of total energy will be delivered for each irradiation point. An independent researcher will be responsible for controlling the on or off phototherapy device because therapists and patients will be blinded to the procedure. The applicator researcher and patient will be wearing eye protection devices. The CON group will be subjected to the same procedures as the groups subjected to the PHO intervention. The phototherapy device to be used is shown in Fig. 2. All parameters of the phototherapy device are shown in the Table 1.

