### Outcome parameters

The outcome parameters described below will be evaluated at baseline and 24 h after the last day of the experimental protocol.

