### Statistical analysis

Pain will be the primary endpoint and will be determined using a VAS, an algometer, the FIQ, and the McPQ. Quality of life as assessed by SF-36, salivary serotonin level, and overall parameters of pain will be secondary endpoints. Statistical analysis will be performed using IBM SPSS software (version 13.0; IBM, Armonk, NY, USA), and a two-sided *P* value <0.05 will be considered significant. The intragroup and intergroup comparisons will be carried out with two-way repeated-measures analysis of variance with post hoc Bonferroni correction or the Kruskal-Wallis test with a post hoc Dunn test. The choice of tests will be based on the distribution (normal or non-normal) of the data by the Shapiro–Wilk test. For categorical data, χ^2^ statistics will be used.

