### Ethical approval

The ethics committee of the Nove de Julho University (Sao Paulo, Brazil) reviewed and approved this study protocol (protocol number 419.828/2013). The trial was conceived and will be conducted according to the principles set forth in the Declaration of Helsinki [32]. All patients will be requested to provide written informed consent prior to randomization, using standard forms. Patients may withdraw from the study at any time without penalty. Our standpoint is that any intervention has beneficial effect. It is an ethical issue in which the control group knows the positive results of the study. Therefore, the control group will be given the opportunity to receive intervention after the end of the trial. The trial is registered at ClinicalTrials.gov under the number NCT02279225 (27 October 2014).

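### All four arms attend about 20 planned sessions, but the VAS is recorded only at baseline and once after treatment, so a woman who leaves early and is not recalled has no post-randomisation VAS

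*Protocol article*

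**What the plan says.** The abstract (Methods/Design) states "The trial will last 10 weeks" and that "the following outcomes will be evaluated on two separate occasions". The body agrees on the number of occasions. Outcome parameters says the outcomes "will be evaluated at baseline and 24 h after the last day of the experimental protocol". Interventions says "the research will record outcome parameters at baseline prior randomization and 48 h after the last day of intervention". The two sections differ on 24 h or 48 h and need reconciling, but both give one occasion before randomisation and one after treatment. The sections on the VAS and on salivary serotonin describe change from randomisation to the end and add no visit in between.

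On attendance, Interventions says "patients will undergo two sets of phototherapy, exercise, or placebo procedures per week". Randomization, blinding, and experimental groups gives the control and exercise arms a switched-off device, and Phototherapy adds: "The CON group will be subjected to the same procedures as the groups subjected to the PHO intervention". Every arm therefore comes to the sessions.

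On the endpoint, Statistical analysis says: "Pain will be the primary endpoint and will be determined using a VAS, an algometer, the FIQ, and the McPQ". The analysis is a two-way repeated-measures ANOVA with Bonferroni correction, or Kruskal-Wallis with Dunn's test if the data are not normal. On leaving, Ethical approval says: "Patients may withdraw from the study at any time without penalty". The article describes no assessment at early exit.

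**The concern.** The trial sees each woman about 20 times during treatment and takes none of those opportunities to record pain. Two things follow for the VAS.

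First, the only post-randomisation value falls after the last session. A woman who stops in, say, week 6 and does not return has a baseline and nothing else. With two time levels, a repeated-measures ANOVA drops her, and Kruskal-Wallis on post-treatment or change values has nothing to rank. In a trial of 60 women in four arms, a few such losses matter. The arms also differ in what they ask of the women (exercise or sham only), so losses need not be balanced.

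Second, the VAS is a single mark on a 10 cm line, so its post-treatment value carries the full occasion-to-occasion variation of a fluctuating symptom.

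A statistical analysis plan can choose a model or an imputation method, but it cannot recover on-treatment values that were never collected. The schedule is therefore a protocol matter.

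**Working it through.** **Schedule count (from the article).** 10 weeks × 2 sessions = 20 planned sessions. There are 2 outcome occasions, 1 of them after randomisation. A woman who leaves before the end and is not recalled has 0 post-randomisation VAS values.

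**The plan's own figure.** The only sample-size calculation is a precision formula for a prevalence: (1.96 × √(0.8 × 0.2) / 0.1)² = 61.47, or 62 rounded up, against 60 stated. It gives no pain difference, SD, correlation or dropout allowance, so everything below rests on stated assumptions.

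**Loss of women (assumed rates).** If 10%, 20% or 30% leave early and are not recalled, 6, 12 or 18 of the 60 have no post-randomisation VAS.

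**Precision (illustrative).** Assumptions:
- SD 1 at each occasion, and a true difference of 0.8 SD between two arms.
- Correlation 0.5 between baseline and any later reading.
- Correlation w between late-treatment readings.
- 15 per group (60/4). The article also says 20 per group, which would make 80 in four groups.
- One two-sided comparison at 0.05, by noncentral t with 28 degrees of freedom.

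For two arms, the group-by-time test with two time levels is the t-test on change. For the mean of k late readings, let m = w + (1 − w)/k, with m = 1 for a single reading.
- Variance of change = m + 1 − 2 × 0.5 = m.
- Variance after baseline adjustment = m − 0.5² = m − 0.25.
- Noncentrality = 0.8 / √(2 × variance / 15). For the single reading this is 0.8/√(2/15) = 2.19 for change and 0.8/√0.10 = 2.53 after adjustment.

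| Post value | m | Power, change | Power, baseline-adjusted |
|---|---|---|---|
| One reading | 1.000 | 0.56 | 0.68 |
| Mean of 4, w = 0.9 | 0.925 | 0.60 | 0.73 |
| Mean of 4, w = 0.8 | 0.850 | 0.63 | 0.78 |
| Mean of 4, w = 0.7 | 0.775 | 0.67 | 0.83 |
| Mean of 4, w = 0.6 | 0.700 | 0.71 | 0.88 |

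With five readings (four in weeks 9-10 plus the final one), m runs from 0.92 (w = 0.9) to 0.68 (w = 0.6), and baseline-adjusted power from 0.73 to 0.90. The four-reading figures are thus slightly conservative for that mean.

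**With Bonferroni.** Six pairwise comparisons give α = 0.05/6 = 0.0083. Power for change is then 0.28 with one reading and 0.34 to 0.43 with the mean of four (w = 0.8 to 0.6).

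**Reading the table.** Baseline adjustment alone (0.56 to 0.68) needs no new data and gains about as much as averaging does under the analysis of change (0.60 to 0.71).

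**The case against.** The strongest case against is that a baseline and end-of-treatment design is ordinary, is stated consistently apart from 24 h or 48 h, and matches the aim of measuring change to week 10. That stands. Values that were never planned are not collected, but they are not thrown away, and nothing here is a contradiction.

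A reader might infer that every early leaver is lost and that the trial compares completers only. The article does not establish this. It says women may withdraw, names no analysis set, and does not say that those who stop treatment go unassessed at week 10. The full protocol may provide for recall. The article's clearer pointer to a completer comparison is the exclusion for more than three absences, and extra VAS readings do not remove it.

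A reader might also infer that one reading carries the primary result. It does not. Pain is measured on four instruments, the algometer is read at several points, and the FIQ covers several symptoms. The single-mark argument applies to the VAS alone, and the remedy leaves the other three instruments as they are.

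Two further objections stand. The gain depends on assumed correlations and is small if late readings correlate at 0.9. And making an on-treatment average the primary measure, while Trial status says women are already being allocated, would mix two endpoint definitions and move the target from post-treatment to on-treatment pain. Self-ratings by women who know whether they exercise also stay open to expectation, whoever handles the form.

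What the objections do not answer is that on-treatment values cannot be created afterwards, and collecting them costs little.

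**Conclusion.** The point holds as a worthwhile improvement limited to the VAS. About 20 planned contacts per woman yield one post-randomisation VAS, and none for a woman who leaves early and is not recalled. The planned two-level analysis cannot then use her.

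The number of women affected is unknown: 6 to 18 of 60 under assumed losses of 10% to 30% without recall. On precision, under the stated assumptions, using the baseline already collected raises power for one uncorrected comparison from 0.56 to about 0.68. Averaging late readings would bring it to about 0.73 to 0.88, and all values fall under the planned Bonferroni correction. The averaging gain belongs to a supportive late-treatment mean. At the post-treatment time point itself, the gains are baseline adjustment and keeping women with partial data.

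**What to change.** For women still to be treated, add a brief self-completed VAS at existing sessions, at least in weeks 9-10 and at the last session attended, passed unread to the blinded assessor. Because the last session is often not known in advance, recording at every session is the surest way to capture it.

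Keep the post-treatment VAS as the primary time point, with its timing settled at one value. Analyse all randomised women with a mixed model that uses every recorded VAS value, with baseline VAS as covariate. Women already treated enter with the values they have. Report the late-treatment mean (four pre-session readings in weeks 9-10 plus the final reading) as a supportive analysis.

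Cost: about one minute per session, somewhat more data entry and a protocol amendment, with no extra visit or device. The benefit is only partial for women already treated, and nothing changes for the McPQ, FIQ or algometer. The mixed model relies on losses being explained by the recorded values, and a woman with no session reading at all still contributes no post-randomisation VAS.

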**Discussion:**

This is the first randomized controlled trial in which the role of phototherapy, exercise training, and a combination of these interventions will be evaluated for chronic pain in patients with FM and TMD. The results will offer valuable clinical evidence for objective assessment of the potential benefits and risks of procedures.

**Trial registration:**

ClinicalTrials.gov Identifier: NCT02279225. Registered 27 October 2014.

## Background

Fibromyalgia (FM) is a chronic syndrome characterized mainly by pain, nonrestorative sleep, fatigue, morning stiffness, depression, and cognitive disorders [1, 2]. Patients with FM often show widespread pain in the presence of tender points (expressed as mild or greater tenderness), which provide the most sensitive, specific, and accurate criteria for making the diagnosis [1, 3]. Using this classification, almost all patients with FM are women because they have more tender points than do men [4]. Overall, FM symptoms lead to significant reduction in functional capacity and quality of life [2, 5, 6]. Developing treatment teams is useful, including clinicians with expertise in patient education, exercise training interventions, and cognitive behavioral therapy [7–9]. An optimized treatment can be provided using the following steps: (1) overall recommendation (e.g., patient education), (2) nonpharmacologic (e.g., exercise, cognitive behavioral therapy, alternative medicine, and central nervous system neurostimulatory intervention), and (3) pharmacologic (e.g., tricyclic complexes, gabapentinoids, γ-hydroxybutyrate, naltrexone, cannabinoids, selective serotonin reuptake antagonists, nonsteroidal anti-inflammatory drugs, and opioids) [4].

A key issue is the association of FM with other musculoskeletal comorbidities, such as temporomandibular dysfunction (TMD) [5]. It has been shown that TMD can develop as a result of mandibular compression during daily living activities and sleep in the patients with FM [5–7], in which the coexistence of these pathologies generates a clinical outcome of high complexity [8]. Unfortunately, no published studies of patients with FM and TMD have evaluated an effective pharmacologic and/or nonpharmacologic therapeutic intervention. Previous studies have examined only the role of different interventions in the situation of a pathology per se. In this issue, exercise training is highly recommended in the controlling of patients with FM. Aerobic, strength, and mixed training programs (combination of aerobic, strength, and flexibility) were shown to reduce pain, number of tender points, fatigue, depression, and anxiety and to improve health-related quality of life as well as functional capacity [9, 10]. Exercises targeted for the face are also indicated for treatment of TMD as a procedure combined with other therapies (e.g., electrotherapy, physiotherapy, temporomandibular joint mobilization, and facial massage) to improve pain sensitivity [11–13].

Phototherapy, such as low-level laser therapy (LLLT) and light-emitting diode (LED) therapy, are recently developed options to treat FM and TMD [14]. LLLT is assumed to modulate several signaling pathways and physiologic mechanisms involved in analgesia [15–17]. This therapeutic approach seems to increase β-endorphin levels, lymphatic flow, and blood supply. Moreover, LLLT is reported to reduce bradykinin, histamine release, swelling, pain-associated molecules, and inflammation phase and to induce muscle relaxation [18, 19]. Similar results have been shown with LED therapy, which has a minor cost and better equipment durability [20].

A comprehensive review of the literature revealed no studies evaluating the role of phototherapy with multiple light sources (LLLT and LED) on the same device in the pain condition in patients with FM and TMD. In addition, there are no prior data involving a combined intervention of phototherapy and exercise training in patients with FM and TMD. The hypothesis of the proposed study is that combined intervention is capable of improving chronic pain in patients with FM and TMD. Knowledge regarding the clinical effects of these interventions can contribute to improved rehabilitation and quality of life among such patients.

### Objective

In this trial, we seek to assess the potential role of exercise training plus phototherapy to reduce chronic pain in women with FM and TMD.

## Methods/Design

### Study design

The EXTRAPHOTO trial (ClinicalTrials.gov identifier NCT02279225) is a multicenter randomized controlled clinical trial comparing the use of exercise training, phototherapy, and exercise training plus phototherapy for pain control in women with two comorbidities (FM and TMD). As part of a simultaneous recruitment process, in the EXTRAPHOTO trial we will identify participants with target disorders in a database of the Unified Health System of Sao Paulo, Brazil. A preliminary analysis showed that patients at three centers with FM specialties are eligible: (1) the Rheumatology Clinic of Nove de Julho University, Sao Paulo, Brazil; (2) the basic health center of Sao Paulo, Brazil; and (3) the basic health center of Sao Paulo in Sao Bernardo do Campo, Brazil. The study procedure will follow the guidelines of the Consolidated Standards of Reporting Trials statement. All participants will receive data on the study aims and experimental procedures. We will obtain signed, written informed consent forms from each patient before inclusion in the study. The trial scheme is detailed in Fig. 1.

**Fig. 1 Fig1:**
[figure not shown]
Trial scheme. CON, Control; EXT, Exercise training; PHO + EXT, Phototherapy plus exercise training; PHO, Phototherapy

### Population and sample size

In a literature review, we found that FM prevalence is higher in women between ages 35 and 60 years than in men [21]. All women patients aged ≥ 35 years and referred for FM and TMD diagnostic evaluation were eligible for inclusion in the present trial. Patient eligibility comprises an evaluation of medical history, physical examination, and dental and rheumatologic routine evaluations. Moreover, patients had to have undergone FM screening as reported by the American College of Rheumatology using the Fibromyalgia Impact Questionnaire (FIQ) 1. The TMD diagnosis had to be reported on the basis of TMD research diagnostic criteria (axes I and II) [22]. The sample size calculation was based on a previous study by Consalter et al. [23] in which the TMD prevalence was 80 % in patients with FM. A 95 % reliability and a 10 % error rate was assumed to estimate the sample size (n) as follows [24]:$$ n={\left(\frac{z_{a/2}\sqrt{p\left(1-p\right)}}{\varepsilon}\right)}^2={\left(\frac{1.96\ast \sqrt{0.8\ast 0.2}}{0.1}\right)}^2 $$

A total of 60 women will be randomized for this trial, with 20 women allocated per group.

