### Recruitment and inclusion criteria

The recruitment methods include direct referral of patients who consult for FM, in which TMD also will be investigated. A rheumatologist and a dentist will make the diagnoses of FM and TMD, respectively. A physician at each FM medical center will participate. A compatible diagnosis of FM will be obtained on the basis of evaluation criteria similar to those previously well defined [25]. The recruitment of 60 patients is planned to be finished within 24 months. Inclusion criteria are as follows: women ≥ 35 years of age presenting with at least a 5-year diagnosis of FM and TMD, optimized drug treatment, cognitive independence to respond to inquiries, functionally independent regarding daily physical activity, availability and ability to fully comply with the training process and phototherapy, and no contraindication to the research procedures. All centers will be informed about the EXTRAPHOTO trial and its inclusion criteria during department meetings. Exclusion criteria are patients in a prior regular and structured physical activity program; missing more than three times from treatment; presence of psychiatric disorders, missing teeth, and/or use of dentures; a history of trauma to the face; currently undergoing orthodontic intervention; and any contraindication to exercise or phototherapy. The FM symptoms can be confused with other disorders. Thus, women for whom there are suspicions of any of the following disorders will be excluded: osteoarthritis, bursitis, tendinitis, rheumatoid arthritis, palindromic rheumatism, polymyalgic rheumatic disease, hydroxyapatite crystal diseases, systemic lupus erythematous, dermatomyositis-polymyositis complex, Lyme disease, hypothyroidism or hyperthyroidism, hyperparathyroidism, previous history of hepatitis, and history for Epstein-Barr virus infection. Sjögren, McArdle, Addison, Cushing, and paraneoplastic syndromes will also be exclusion criteria.

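### The sample size rests on a formula for estimating TMD prevalence, which has no link to the four-group comparison of pain that the trial makes

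*Protocol article*

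**What the plan says.** Under Population and sample size, the protocol article bases the calculation on an earlier study "in which the TMD prevalence was 80 % in patients with FM". A 95 % level and a 10 % "error rate was assumed to estimate the sample size (n) as follows": n = (1.96·√(0.8·0.2)/0.1)², without printing the result. The next sentence reads "A total of 60 women will be randomized for this trial, with 20 women allocated per group".

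The rest of the article describes a different task:

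- **Groups.** In the abstract's Methods/Design, "patients will be randomly allocated to one of four groups".
- **Entry.** Recruitment and inclusion criteria admits women "presenting with at least a 5-year diagnosis of FM and TMD".
- **Endpoint.** Statistical analysis states: "Pain will be the primary endpoint and will be determined using a VAS, an algometer, the FIQ, and the McPQ".
- **Analysis.** The same section plans two-way repeated-measures ANOVA with post hoc Bonferroni correction, or Kruskal-Wallis with Dunn's test, at a two-sided 0.05 level.
- **Total.** Recruitment and inclusion criteria repeats the total: "The recruitment of 60 patients is planned to be finished within 24 months".

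**The concern.** The formula sizes a survey that asks what share of fibromyalgia patients have TMD. In this trial that share is 100% by the entry criteria, so there is nothing to estimate. The quantity that decides whether the trial is large enough is the between-group difference in pain relative to its variability, and this does not enter the calculation.

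The article does not merely leave this to another document. It gives a basis for the number, and that basis is for the wrong quantity. A separate analysis plan could add a power statement but could not make the printed justification valid.

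At stake is the reading of the result. Someone who sees a worked formula may assume that the number was derived for the trial's question, and may take a non-significant pain contrast as evidence of no effect.

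**Working it through.** **1. The printed formula.** Inputs from Population and sample size: z = 1.96, p = 0.8, ε = 0.1.

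n = (1.96 × √0.16 / 0.1)² = (1.96 × 0.4 / 0.1)² = 7.84² = 61.47.

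At n = 60 the half-width is 1.96 × √(0.16/60) = 0.1012, that is 10.12 points instead of 10. The stated 60 is therefore the formula's result after loose rounding.

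**2. What the formula contains.** It has a prevalence, a confidence level and a precision margin. The 10 % is the half-width of an interval for a proportion, not a type II error, so it does not imply 90% power. There is no pain difference, SD, power or number of groups.

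**3. The group sizes.** Four groups of 20 make 4 × 20 = 80. A total of 60 over four groups is 60/4 = 15 each. Twenty per group gives 60 only with three groups. Both sizes are carried below because the article does not settle which is meant.

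**4. What each size could detect (illustration).** The article gives no target difference or SD, so no required sample size can be derived for pain. The standardised difference detectable between two groups can be computed.

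Assumptions:

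- 80% power, two-sided 5%, normally distributed data.
- Error degrees of freedom pooled over four groups: 4 × 14 = 56 or 4 × 19 = 76.
- No gain from the baseline measurement.
- The number of Bonferroni comparisons is not stated. Three (each active group against control) and six (all pairs, 4 × 3/2) are both assumed.

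To close approximation d = (t₁₋α/₂ + t₀.₈₀) × √(2/n). For 15 per group, unadjusted: (2.003 + 0.848) × √(2/15) = 2.851 × 0.365 = 1.04. The table uses the noncentral t distribution.

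| Per group | Unadjusted | Three comparisons | Six comparisons |
|---|---|---|---|
| 15 | 1.04 SD | 1.21 SD | 1.31 SD |
| 20 | 0.90 SD | 1.04 SD | 1.13 SD |

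**5. Effect of the baseline measurement.** With two time points, the group-by-time test is a test of change. Relative to a single post-treatment value, the detectable difference is multiplied by √(2(1 − ρ)), where ρ is the baseline correlation (assumed; none is given):

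- ρ = 0.5: √1.0 = 1, no change.
- ρ = 0.7: √0.6 = 0.77, about a fifth lower; 1.04 SD becomes about 0.81.
- ρ = 0.3: √1.4 = 1.18, about a fifth higher; 1.04 SD becomes about 1.23.

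**6. On the VAS.** If the SD were 1.5 to 2.5 cm (assumed), 15 per group would detect 1.04 × 1.5 = 1.6 cm to 1.04 × 2.5 = 2.6 cm unadjusted. Over six pairs it would detect 1.31 × 1.5 = 2.0 cm to 1.31 × 2.5 = 3.3 cm.

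**The case against.** The article says openly that its calculation rests on TMD prevalence and never claims that 60 was sized for pain. That is true, and it means the fault lies in the choice of basis, not in a false statement about power. It does not rescue the basis, which is the only one given for a randomised comparison.

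The detectable differences depend on assumptions the article does not supply: the baseline correlation, the number of Bonferroni comparisons, and parametric analysis. This also stands. The figures are an illustration and move by about a fifth either way with the correlation.

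Rewriting the justification adds no patients and no power, and allocation is already under way according to Trial status. That is correct. What the change improves is how the result can be read.

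Three stronger readings are tempting, and the documents do not support them:

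- **That 60 is an arithmetic error because the formula gives 61.47.** The article prints no result, and the gap moves the margin by 0.12 points. This is rounding and not a separate error.
- **That the trial is shown to be underpowered.** Without a target difference and an SD, neither adequate nor inadequate power can be established. It can be said only that the stated basis does not address the question.
- **That the number was really set by feasibility, at 15 per group.** The article gives a 24-month recruitment window but no such rationale, and it nowhere states 15.

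**Conclusion.** The point holds. The stated basis for the sample size is the precision of a prevalence that the trial does not estimate, and it bears no relation to the comparison of pain across four groups. This follows from the article's own text and needs no assumption.

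The size of the consequence does need assumptions. Under those listed, only differences of roughly 0.9 to 1.3 SD would be detected with 80% power, depending on group size and multiplicity. With baseline correlations from 0.3 to 0.7 the range widens by about a fifth at each end. The group size itself is unsettled, because the total of 60 and 20 per group cannot both hold with four groups.

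**What to change.** Rewrite the sample size paragraph in this order:

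1. Remove the prevalence formula as the justification for the number randomised.
2. State the true basis for the number, whatever it was.
3. Reconcile the total of 60 with 20 per group, given four groups. This must come before any detectable difference is stated.
4. Name one primary pain measure out of the four listed. For it, give the difference detectable at the reconciled size under the planned analysis, with the assumed SD and its source, the baseline correlation and the number of Bonferroni comparisons.
5. State that contrasts will be read from confidence intervals and that non-significant ones are inconclusive.

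The cost is one rewritten paragraph and a justification that reads less favourably. No extra patients are needed if 60 is confirmed as the total; if 20 per group is what was meant, the total becomes 80.
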